### Misuse / overdose

Any IMP misuse/or overdose associated or not with any AE should be reported on an Adverse Event form and faxed or emailed to the Principal Investigator (see Section 10.5.4).

## IMP accountability

The Principal Investigator will provide specific forms for drug accountability, which will be kept up-to-date by the Investigator and/or Hospital Pharmacist throughout the study.

The accountability forms should be filed in the ISF*.* The CRA will verify the drug accountability forms for completeness and accuracy at each site visit.

At the end of the study, delivery records should be reconciled with dispensing and used/unused records. Any discrepancy must be accounted for.

Used/unused IMP should be kept in a secure place at the site until the records have been verified by the CRA.

## Randomization codes and procedures for blinding

Not applicable.

# PRIOR AND CONCOMITANT MEDICATION

## Prior medication

The term ‘prior medication’ refers to any medication given before study entry, i.e. before informed consent signature.

All relevant prior medication taken within 30 days before inclusion must be recorded in the patient’s medical records and documented on the appropriate pages of the eCRF.

Non-inclusion criteria related to prior medication are:

1. Prior radiotherapy or chemotherapy.
2. Prior vaccinations and immunosuppressants within 30 days prior to starting the study
3. Concurrent treatment with a non-permitted drug.

All authorized medications taken regularly at baseline will be continued and documented as a concomitant medication throughout the study protocol.

In order to mitigate infusion‑related reactions, a premedication with an antihistamine and with paracetamol (acetaminophen) 30 to 60 minutes prior to the first 4 infusions of avelumab is mandatory (for example, 25‑50 mg diphenhydramine and 500‑650 mg paracetamol IV or oral).

Premedication should be administered for subsequent avelumab infusions based upon clinical judgment and presence/severity of prior infusion reactions. This may be modified based on local treatment standards and guidelines, as appropriate.

Avelumab should be administered in a setting that allows for immediate access to an intensive care unit or equivalent environment and administration of therapy for anaphylaxis, such as the ability to implement immediate resuscitation measures. Steroids (dexamethasone 10 mg), epinephrine (1:1,000 dilution), allergy medications (IV antihistamines), bronchodilators, or equivalents, and oxygen should be available for immediate access.

Following avelumab infusions, patients must be observed for 30 minutes post‑infusion for potential infusion‑related reactions.

## Concomitant medication

The term ‘concomitant medication’ refers to any medication that the patient receives at any time during the study, i.e. from study entry to the last study visit. This includes the screening/baseline period, treatment period and follow-up as defined in the protocol.

Concomitant medication should be avoided as much as possible during the study. However, if it is considered to be necessary for the patient’s welfare or well-being and is unlikely to interfere with the study assessments, it may be given at the discretion of the Investigator, preferably after consultation with the Principal Investigator. The decision to withdraw a patient on the basis of concomitant medication should preferably be made jointly by the Principal Investigator and the Investigator.

The following treatments will be more specifically tracked in the eCRF and will be administered in accordance with the following recommendations:

- Anti-emetics
- Week 3 (D15) ± 3 days – start of mFOLFOX-6 chemotherapy protocol
  - Oxaliplatin 85 mg/m2 in a 2-hour infusion
  - Leucovorin 400 mg/m2 over 2 hours
  - 48-hour infusion of fluorouracil 2,400 mg/m²
- mFOLFOX-6 chemotherapy protocol is given with avelumab in a successive manner such that mFOLFOX is administered 30-minutes after avelumab has already been administered every 2 weeks ± 3 days (weeks 3, 5, 7, 9, 11 and 13)

All concomitant medications must be recorded in the patient’s medical records and documented in the appropriate pages of the eCRF

# STUDY PLAN

The method for assessing each study parameters is described in Section 10. .

Investigators may also refer to the study flowchart (Table 1).

## 8.1. Patient recruitment

### Informed Consent

The Investigator should provide each patient with relevant, comprehensive, verbal and written information regarding the objectives and procedures of the study as well as the possible risks involved. A patient information sheet will be given to the patient.

The patient should have enough time and opportunity to inquire about study details. All his/her questions should be answered in a clear manner. The patient must be informed about his/her right to withdraw from the study at any time.

Signed informed consent must be obtained from the patient prior to undertaking any study-related procedure. If possible, informed consent must be obtained from the patient.

Two original copies of the informed consent form should be signed and dated by the patient (or the designated person as described above) and the Investigator. One original fully signed copy should be given to the patient (or the designated person as described above). The Investigator will keep the other copy. The process for obtaining consent will be documented in the patient’s file.

### Patient enrolment

The patient is considered as enrolled when informed consent has been signed by the patient.

### Patient allocation

All patients fulfilling all inclusion and none of the exclusion criteria will be considered as eligible.

Eligible patientswill receive a short-course radiation therapy followed by 6 cycles of mFOLFOX-6 chemotherapy plus avelumab every 2 weeks ± 3 days. Two to three weeks after the last cycle of chemotherapy plus avelumab, the patient will undergo a TME, depending on the patient’s condition and laboratory exams.

Study treatment units will be allocated sequentially in chronological order of inclusion in ascending order.

### Replacement of early withdrawals

No replacement of early withdrawal will be performed.

## 8.2. Schedule of visits

The study flowchart (Table 1) lists all of the assessments and indicates with an “X”, the visits when they are performed. All data obtained from these assessments must be supported in the patient’s source documentation.

After enrolment, all patients will be treated with IMP. The start of radiation therapy corresponds to D1 (week 1), and IMP administration at D15 ± 3 days (week 3).

During all visits, all relevant data are to be collected in the eCRF.

### 8.2.1. Selection/patient recruitment: visit 1

Patients who fulfil the eligibility criteria will be informed of all details concerning the study. Only those who agree to participate in the study and sign the informed consent will be enrolled.

Study-related procedures such as IMP administration can be only undertaken after the obtainment of the informed consent.

The visit procedures are as per the following points:

- - 1. Informed consent
    2. Verification of selection criteria
    3. Patient number:
    - Each patient in the study is uniquely identified by a 6-digit patient number which is a combination of his/her 3-digit center number and 3-digit subject number.
    - The center number is assigned by the Principal Investigator to the investigative site.
    - Upon signing the informed consent form, the patient is assigned a patient number by the Investigator.
    - At each site, the first patient is assigned patient number 1, and subsequent patients are assigned consecutive numbers (e.g. the second patient is assigned patient number 2; the third patient is assigned patient number 3).
    1. Medical history
    2. Physical examination/vital signs/weight
    3. Laboratory tests:
    - Hematology assessments: complete blood count (CBC)
    - Blood chemistry: blood urea nitrogen (BUN), creatinine, electrolytes, SGPT, SGOT, GGT, alkaline phosphatase, bilirubin
    - Virology:
      - - HBV surface antigen and HCV antibodies
        - Conduct of HCV PCR for patients positive for HCV antibodies (to differentiate active infection from past infection with HCV)
    - Urine or serum pregnancy test for women of childbearing potential who are sexually active
    - Free T4 and TSH
    - Tumor markers (CEA and CA 19-9)
    1. Baseline biopsy to evaluate:
    - PD-L1 expression:
      - - Will be evaluated on tumor cells and infiltrating immune T cells.
        - Will be classified as negative or positive or not applicable (categorical variable).
    - CD4+, CD8+ and CD3+ T cell infiltration:
      - - Will be quantified in mm2 in the most abundant tumor-infiltrating area in both, the stroma and the tumor, of the baseline biopsy (continuous variable).
        - After the recruitment of around 5 patients, a cut-off value will be agreed upon and the numerical values corresponding to T cell infiltration (continuous variable) will then be classified as low or high or not applicable (categorical variable).
    - Microsatellite instability (MSI or MMR status):
      - - Will be evaluated once on either the baseline biopsy or D10 biopsy.
        - The MSI predictive markers to be assessed are: MLH-1, MSH-2, MSH-6, and PMS-2.
    1. Prior treatment (within the 30 previous days).
    2. Imaging: pelvic MRI (rectal protocol), CT or PET scan of the chest and the abdomen
    3. Patient-reported outcome: quality of life assessment using FACT-C questionnaire (Lynch BM et al., 2008):
    - The questionnaire is available in Arabic and English versions.
    - It should be completed by the patient in Arabic, or in English in case he/she does not understand Arabic.
    - Once completed, the site staff will do the data entry in the eCRF.
    - The average time to complete the questionnaire is 5 to10 minutes.
    - FACT-C is a 36-item quality-of-life questionnaire with five subscales: physical well-being (PWB), social/family well-being (SWB), emotional well-being (EWB), and functional well-being (FWB), and colorectal cancer-specific additional concerns (colorectal cancer subscale, CCS).
    - Participants rate how they have felt over the past 7 days, on a 5-point Likert scale ranging from 0 (not at all) to 4 (very much).
    - The total FACT-C score is obtained by summing individual subscale scores (PWB + EWB + SWB + FWB + CCS).
    - The overall quality-of-life score can range from 0 to 136 (two items relevant only to stoma patients are not included in the score).
    - Higher scores indicate better quality of life.
    - Each subscale has a maximum score of 28, except for the emotional well-being subscale, which has a maximum of 24.

### 8.2.2. Radiation therapy period: visits 2 to 7

The procedures to be done for 5 days from D1 to D5 during week 1 (visits 2 to 6) are as follows:

- - 1. Short-course radiation therapy:
    - **Treatment technique:**
      - Either 3D conformal or intensity-modulated radiotherapy (IMRT) treatment planning may be used on this study.
      - Both techniques are approved, so either technique may be used.
      - Fields should be chosen to minimize dose to organs at risk (small bowel, femoral heads, and bladder).
      - Multiple beam techniques, both coplanar and non-coplanar may be used to achieve the objective.
      - CT with immobilization is required for planning.
      - Patients are to be placed in a position that best suits the technique used and ensures immobilization and displacement of normal tissues.
      - The slice thickness must be no greater than 5 mm, and the Gross Tumor Volume (GTV), Clinical Target Volume (CTV), and Planning Target Volume (PTV) must be defined on all axial CT slices.
      - Data on radiation technique and parameters should be made available for review at the beginning or completion of radiation therapy.
    - **Equipment:**
      - High energy X-rays with nominal energy of 6 MV (IMRT) or 15 MV (3D) should be used.
      - Image guidance (cone beam) should be used on daily basis.
    - **Target volume definitions.**
      - Volume definition and contouring will be done on planning CT scans.
      - Use of contrast enhanced MRI for better target delineation is encouraged.
      - GTV must include all primary tumor extent, and enlarged lymph nodes.
      - CTV includes GTV with 0.5 cm extension and all perirectal, presacral, and internal iliac lymph nodes all the way up to the sacral promontory.
      - PTV is a 1cm expansion of the CTV in all directions.
      - Adjustments of PTV anteriorly could be made to reduce incidental radiation to the bladder and bowel.
    - **Target dose:**
      - The daily dose will be 5 Gy to a total dose of 25 Gy.
      - Dose will be prescribed to an isodose surface that encompasses the PTV and allows the dose uniformity requirements of ≤5%.
      - Dose is specified in Gy to muscle.
      - Density corrections are required as all patients will be treated using CT-based planning.
    - All radiation plans should be submitted for audit to AUBMC.
    1. Adverse event collection

The procedures to be done at D10 during week 2 ± 3 days (visit 7) are as follows:

- - 1. Sigmoidoscopy
    2. Biopsy to evaluate:
    - PD-L1 expression:
      - - Will be evaluated on tumor cells and infiltrating immune T cells.
        - Will be classified as negative or positive or not applicable (categorical variable).
    - CD4+, CD8+ and CD3+ T cell infiltration:
      - - Will be quantified in mm2 in the most abundant tumor-infiltrating area in both, the stroma and the tumor, of the D10 biopsy (continuous variable).
        - After the recruitment of around 5 patients, a cut-off value will be agreed upon and the numerical values corresponding to T cell infiltration (continuous variable) will then be classified as low or high or not applicable (categorical variable).
    - Microsatellite instability (MSI or MMR status):
      - - Will be evaluated once on either the baseline biopsy or D10 biopsy.
        - The MSI predictive markers to be assessed are: MLH-1, MSH-2, MSH-6, and PMS-2.
    - Image of the biopsy is to be provided.
    1. Concomitant medications
    2. Adverse event collection

### 8.2.3. Treatment period: visits 8 to 13

The procedures to be done from week 3 ± 3 days to week 13 ± 3 days (visits 8 to 14), starting D15 are as follows:

- - 1. Physical examination/vital signs/weight
    2. Laboratory tests:
    - Hematology assessments: CBC
    - Blood chemistry: BUN, creatinine, electrolytes, SGPT, SGOT, GGT, alkaline phosphatase, bilirubin
    - Urine or serum pregnancy test for women of childbearing potential who are sexually active
    - Free T4 and TSH
    1. Concomitant medications including mFOLFOX-6 chemotherapy protocol and anti-emetics:
    - Oxaliplatin 85 mg/m2 in a 2-hour infusion
    - Leucovorin 400 mg/m2 over 2 hours
    - 48-hour infusion of fluorouracil 2,400 mg/m2
    1. IMP administration: avelumab 10 mg/kg first administration at D15, then every 2 weeks for 6 cycles
    2. Adverse event collection
    3. Patient-reported outcome: quality of life assessment using FACT-C questionnaire

### 8.2.4. End of treatment visit including study completion and premature withdrawal: visit 13

Besides the procedures to be done at week 13 ± 3 days, tumor markers (CEA and CA 19-9) should be assessed at the end of treatment. Also, at the time patients discontinue the study treatment, a visit should be scheduled as soon as possible, but no later than 14 days from the last day of study medication, at which time all of the assessments listed for the End of Treatment visit will be performed. An End of Treatment eCRF page should be completed, giving the date and reason for stopping the study treatment.

### 8.2.5. Surgery: visit 14

Depending on the patient’s condition and laboratory exams, the procedures to be done 2 to 3 weeks ± 3 days after the last cycle of chemotherapy plus avelumab are as follows:

- - 1. Prior to surgery: pelvic MRI (rectal protocol), optional
    2. Frequency, grade, and attribution of surgical complications to the neoadjuvant treatment using the Clavien-Dindo classification (to grade surgical complications).
    3. Laboratory tests:
    - Hematology assessments: CBC
    - Coagulation tests (PT and PTT) should be done a couple of days prior to surgery on week 16 or 17
    - Blood chemistry: BUN, creatinine, electrolytes, SGPT, SGOT, GGT, alkaline phosphatase, bilirubin
    - Urine or serum pregnancy test for women of childbearing potential who are sexually active
    1. Concomitant medications
    2. Adverse event collection
    3. Surgery: TME (open, laparoscopic, or robotic):
    - All TME procedures will be video recorded and the corresponding videotapes and images of the resected specimens are to be made available.
    - Centralized random audit of videos will be performed (Curtis NJ et al., 2017).
    1. Quality assessment and completeness in a TME specimen: all TME specimens are to be processed and graded using the recommendations of the College of American Pathologists (CAP, 2013; Parfitt JR et al., 2007).
    - Specimen handling upon receiving:
      - Paint the non-peritonealized bare areas of the specimen with ink.
      - Open the specimen along the anterior aspect from the top and the bottom, leaving the bowel intact at a level just above and just below the tumor.
      - Place loose, formalin-soaked gauze wicks into the unopened ends of the bowel.
      - Fix the specimen for at least 48 hours.
    - Fixed specimen:
      - Slice through the unopened rectum at 3–5 mm intervals; lay slices down on the work surface.
      - Inspect these slices to note:
        - Extent of tumor and the closest distance of tumor to the CRM (circumferential radial margin, record this distance).
        - Any obviously positive nodes and the distance of any positive node to the CRM (record this distance).
        - Record whether the closest distance of tumor to CRM is anterior, posterior or lateral.
        - Fat away from the tumor must also be examined to detect lymph nodes.
    - Block selection for microscopic examination:
      - Three blocks of tumor showing closest CRM.
      - Two blocks of tumor showing luminal aspect.
      - All lymph nodes (being careful not to double-count nodes present in more than one slice).
      - Any polyps.
      - Proximal and distal resection margins (distal margin includes both mucosa and mesorectum; blocks from mucosal margins may be omitted if tumor is greater than 3 cm away).
    - Completeness of the mesorectum in a total mesorectal excision specimen, as per the criteria of the College of American Pathologists (CAP, 2013):
      - The specimen should be assessed grossly to assess the completeness of the surgery according to the below definition:
      - Complete: Mesorectum is intact and smooth and any defect in surface is not deeper than 5 mm. CRM is smooth and regular.
      - Nearly complete: The mesorectum is irregular however no muscularis propria is visible. CRM is irregular.
      - Incomplete: The mesorectum is little bulk with defects reaching muscularis propria. CRM is irregular.
    1. After the surgery: documentation of whether the patient achieved a pathological complete response defined as no viable tumor cells on the resected specimen.

9) Resected tumor specimen to evaluate:

- - - PD-L1 expression:
      - - Will be evaluated on tumor cells and infiltrating immune T cells.
        - Will be classified as negative or positive or not applicable (categorical variable).
    - CD4+, CD8+ and CD3+ T cell infiltration:
      - - Will be quantified in mm2 in the most abundant tumor-infiltrating area in both, the stroma and the tumor, of the surgical specimen (continuous variable).
        - In case of pathologic complete response, the T cell count corresponding to the tumor area of the surgical specimen will be noted as “not applicable”.
        - After the recruitment of around 5 patients, a cut-off value will be agreed upon and the numerical values corresponding to T cell infiltration (continuous variable) will then be classified as low or high or not applicable (categorical variable).
    - TRG:

The Becker et al. tumor regression grading system will be used to categorize the amount of regressive changes after cytotoxic treatment as follows:1a. No viable tumor/ tumor bed + chemotherapy effect;

1b. <10% viable tumor/ tumor bed + chemotherapy effect;

2. 10-50% viable tumor/ tumor bed + chemotherapy effect;

3. >50% viable tumor/ tumor bed **±** chemotherapy effect.

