## Secondary objectives

The secondary objectives of the study are:

1. To identify the proportion of patients who remain progression free at 3 years.
2. To explore changes in PD-L1 expression and T-cell infiltration.
3. To evaluate the safety and tolerability of mFOLFOX-6/avelumab.
4. To assess the quality of life of the patients in a neoadjuvant setting with avelumab.

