## Endpoints

The primary endpoint is the proportion of patients who achieve a pathological complete response, defined as no viable tumor cells onthe resected specimen.

The secondary endpoints are:

1. Progression-free survival (PFS) at 3 years will be estimated with the Kaplan-Meier method and presented with the 95% confidence interval (CI).
2. Evaluation of response by obtaining Tumor Regression Grade (TRG).
3. Evaluation of biomarkers: CD4+, CD8+ and CD3+ T cell infiltration, and changes in PD-L1 expression.
4. Frequency, severity, and attribution of AEs related to avelumab in neoadjuvant setting.
5. Quality of life assessment using the questionnaire for the functional assessment of cancer therapy for patients with colorectal cancer (FACT-C, English version 4 of 16 November 2007 or Arabic version 4 of 03 September 2014).

TRG system aims to categorize the amount of regressive changes after cytotoxic treatment mostly refer onto the amount of therapy induced fibrosis in relation to residual tumor or the estimated percentage of residual tumor in relation to the previous tumor site (Thies S & Langer R, 2013).

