## Exploratory endpoints

The exploratory endpoints are:

1. Evaluation of biomarkers CD4+, CD8+ and CD3+ T cell infiltration, and changes in PD-L1 expression. This endpoint aims to demonstrate proof of concept that short-course radiation therapy up-regulates PD-L1 expression and induces immune cell infiltration.
2. Serum markers of inflammation: neutrophil/lymphocyte ratio.
3. Quality of life assessed using FACT-C questionnaire (FACT-C, English version 4 of 16 November 2007 or Arabic version 4 of 03 September 2014).

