# STATISTICS

## Statistical analysis plan

The detailed technical aspects of the statistical analyses will be provided in the SAP. The SAP will possibly take protocol amendments into account and adapt to unexpected issues raised by the trial running and/or data that affect planned analyses in the protocol.

Any deviations from the protocol regarding the description of statistical analysis in the SAP will be discussed in the study report.

Prior to locking the database, a data review meeting will be planned to review individual data and validate the SAP.

The distribution of parameters, including safety data, will be summarized using descriptive statistics according to the study variable:

- Categorical variables (binary, nominal and ordinal) will be presented by contingency tables (frequencies and percentages). Number and percentages of missing data will also be mentioned.
- Quantitative variables will be presented by their mean, standard deviation, standard error, median, quartiles and range, minimum and maximum values. The number of documented values will also be mentioned.

The primary endpoint will be presented by number and proportion of patients who achieved pCR along with the one-sided 95% confidence interval. Using Kaplan-Meier method, the median PFS will be estimated along with its 95% confidence interval. Exploratory variables will be analyzed according to their scale of measurement by using mean ± standard deviation or frequency distribution for numeric and categorical variables respectively.

Frequency distribution for AEs and SAEs will be presented per cycle and per patient. Similarly this will be done for the SAE of grade 3 or above combined.

No subgroup analysis is planned.

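### PD-L1 is recorded only as negative, positive or not applicable, which weakens the stated aim of showing that short-course radiotherapy raises its expression

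*Protocol*

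**What the plan says.** - **Scale.** Sections 8.2.1 (baseline), 8.2.2 (day 10) and 8.2.5 (resected specimen) use the same words for PD-L1: "Will be classified as negative or positive or not applicable (categorical variable". The protocol specifies no percentage of stained cells, intensity, combined score or ordinal grade, and no cut-off for positive.
- **Compartments.** The same sections say of PD-L1: "Will be evaluated on tumor cells and infiltrating immune T cells". They do not say whether each compartment gets its own result.
- **Aim.** Section 10.3 states: "This endpoint aims to demonstrate proof of concept that short-course radiation therapy up-regulates PD-L1 expression and induces immune cell infiltration". Section 2.2 has the secondary objective "To explore changes in PD-L1 expression and T-cell infiltration", and section 3.2 lists among the secondary endpoints "Evaluation of biomarkers: CD4+, CD8+ and CD3+ T cell infiltration, and changes in PD-L1 expression".
- **Companion marker.** T-cell infiltration is handled differently in the same visit lists: "Will be quantified in mm2 in the most abundant tumor-infiltrating area". It is held as a continuous variable and grouped into low or high only later.
- **Analysis.** Section 12.1 summarises exploratory variables by mean and standard deviation or "frequency distribution for numeric and categorical variables respectively". It names no hypothesis test for PD-L1.

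**The concern.** Up-regulation is a change in amount, and the recorded variable carries no amount. Two kinds of rise are invisible on this scale: one in a specimen already positive at baseline, and one in a negative specimen that does not reach the cut-off. Only patients who cross the cut-off between the two biopsies contribute evidence of an increase.

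What is at stake is how well the trial can answer its own biological question. The day 10 biopsy comes after radiotherapy and before the first avelumab and mFOLFOX-6 dose, so it is the one specimen that isolates the radiotherapy effect. Section 17 lists the day 10 sigmoidoscopy, biopsy and pathology analysis as trial-specific. A coarse reading gives a less precise answer than the same slide could give. This is a matter of the data captured, which the protocol fixes, rather than of how an analysis plan later treats them.

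**Working it through.** The protocol gives no PD-L1 sample size, power or threshold, so there is no stated figure to reproduce. The check is a logical step followed by two illustrations.

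**1. What the scale can record from baseline to day 10, within one compartment**

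| Baseline | Possible day 10 reading | Can an increase appear? |
|---|---|---|
| Negative | negative, positive, not applicable | Only if the cut-off is crossed |
| Positive | positive, negative, not applicable | No |

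**2. How many patients could show an increase**

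Inputs: N = 36 (primary efficacy set) or 44 (enrolled), both from section 12.2. The baseline positive share b is not in the protocol and is assumed to be 10% to 70%. The number able to show an increase is N × (1 − b), rounded.

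| b | N = 36 | N = 44 |
|---|---|---|
| 10% | 32.4 → 32 can, 4 cannot | 39.6 → 40 can, 4 cannot |
| 30% | 25.2 → 25 can, 11 cannot | 30.8 → 31 can, 13 cannot |
| 50% | 18 can, 18 cannot | 22 can, 22 cannot |
| 70% | 10.8 → 11 can, 25 cannot | 13.2 → 13 can, 31 cannot |

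These counts treat each patient as having one result. They are upper limits on who can contribute, because rises below the cut-off are lost as well.

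**3. Information lost, expressed as power**

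All inputs here are assumptions: 36 pairs, a normally distributed underlying score with baseline SD 1, mean rise 0.5, SD of the within-patient change 0.9, and two-sided 0.05. The continuous score is tested by Wilcoxon signed-rank and the two-level reading by exact McNemar. Power is used only as a yardstick for information. Two variance models were run by simulation:

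- *Added variance:* day 10 = baseline + 0.5 + N(0, 0.9). The day 10 variance becomes 1 + 0.9² = 1.81.
- *Equal variance:* the day 10 variance is held at 1 with the same SD of change. From 0.81 = 2 − 2ρ, the correlation between biopsies is ρ = 0.595.

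| Positive at baseline | Negative/positive, added variance | Negative/positive, equal variance |
|---|---|---|
| 20% | 0.58–0.59 | 0.37 |
| 40% | 0.37–0.41 | 0.45 |
| 60% | 0.14–0.18 | 0.38–0.39 |
| 80% | 0.02–0.03 | 0.18–0.19 |

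The continuous score has power of about 0.87 to 0.91 throughout. Ranges within a cell are the spread over repeated simulations of 1,500 to 4,000 trials.

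The two-level reading is well below the continuous score in every cell, but the pattern across rows depends on the model. Under added variance, power falls steadily over these four shares. Under equal variance it peaks near 40%, and it is lower still at very low positivity (0.20 at 10%, 0.07 at 5%).

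A larger assumed rise of 0.8 SD under added variance narrows the gap at low positivity but does not close it: near 1.00 for the continuous score, against 0.89, 0.79, 0.50 and 0.12 at the four shares.

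**The case against.** **No test is planned.** The objective is worded as exploration, section 10.3 files the endpoint as exploratory (section 3.2 lists it as secondary), and section 12.1 plans only description. Conversion from negative to positive is a legitimate, if coarser, readout. This stands and limits the weight of the point. It does not remove the mismatch, because section 10.3 also speaks of demonstrating proof of concept, and a descriptive table of conversions suffers the same loss.

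**Two compartments are read.** If they are recorded separately, a patient positive on tumour cells could still convert on immune cells. The protocol is silent on this, and the ceiling remains within each compartment.

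**The comparator is idealised.** The continuous score has no floor at zero and no reader error, so the real gain would be smaller if many specimens stain at or near zero. This stands as a caution on the figures.

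A reader might also infer three stronger things that the documents do not support:

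- *That the amount can never be recovered.* The protocol does not say that stained slides are discarded. PD-L1 is read centrally (section 8.3.2), sample details sit in a laboratory manual that is not at hand, and an image of the day 10 biopsy is to be provided. Re-reading may be possible, and the manual may already specify a score.
- *That the day 10 biopsy is largely wasted.* It also yields continuous CD3+, CD4+ and CD8+ values, which serve the other half of the section 10.3 aim, and it may supply MSI status.
- *That power always falls as more tumours are positive at baseline.* This holds over 20% to 80% under one variance model only.

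**Conclusion.** The point holds as a mismatch between aim and scale. The logical part needs no assumption: within a compartment, a baseline-positive specimen cannot register an increase, and sub-threshold rises in negative specimens are lost. The aim is weakened but not made impossible.

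The size is illustrative only. Under the stated assumptions the two-level reading has power of about 0.02 to 0.59 over 20% to 80% baseline positivity, against about 0.87 to 0.91 for a continuous score. The baseline positive share, the mean rise and the variances are all assumed, and the spread across variance models means that no single figure should be relied on. The direction is the same in every case run.

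The consequence is confined to a secondary or exploratory biomarker endpoint. The pCR decision rule, the stage 1 stopping rule and the safety analysis are unaffected. This is a worthwhile, inexpensive improvement and not a threat to the trial's main conclusion.

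**What to change.** In sections 8.2.1, 8.2.2 and 8.2.5, ask the central laboratory to record two further numbers from the same stained slide at baseline, day 10 and surgery: the percentage of PD-L1-positive tumour cells and, separately, the percentage of PD-L1-positive infiltrating immune cells. Keep the negative/positive/not applicable classification. Keep not applicable for the tumour-cell percentage where no tumour cells remain.

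In section 10.3, say that the paired within-patient change from baseline to day 10 in each percentage will be reported alongside the classification. A descriptive summary with a confidence interval would suffice; no formal test is needed.

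The cost is two numeric eCRF fields per specimen, a line in the laboratory manual and slightly more reading time per slide. No additional tissue, staining or procedure is required. If specimens have already been read on the two-level scale, check whether their slides are available for re-reading, so that the percentages cover all patients.
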